### Sampling, randomization, and blinding methods

After selecting the initial samples, the permuted block randomization will be done using a randomized block design with four blocks by a statistics consultant from a valid website (Sealed Envelope.Com or Randomization.Com). Then, the participants will be divided into two groups per the 1:1 allocation ratio. In this way, after listing all possible situations, 75 blocks of 4 will be created based on the sample size of 300 people. Then, by assigning a number to each of them, using a computerized random number table, with a ratio of 1:1, people will be divided into two intervention and control groups. Then, the subjects will be divided into two intervention and control groups. The numbers are placed in sealed envelopes in the order of each block generated. Each eligible patient who enters the room is then given an envelope. After that, they are assigned to one of these groups. Patient information will be recorded by the research team and confidentiality will be respected.

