**Methodology/Design:**

This study entails three steps. The first step includes the systematic review of literature on a health-promoting lifestyle in infertile couples undergoing ARTs, a systematic review of observational studies and interventions in couple’s lifestyle, then, a systematic review of qualitative studies on infertility in couples and their lifestyle, and in the final step couple’s life style literature systematically will evaluate in Iran. In case of failure to obtain the required results from systematic reviews, cross-sectional studies will be carried out to determine the lifestyle of infertile couples receiving ARTs. In the second stage, by holding a panel of experts, an intervention is planned based on the results of the previous stages in order to improve the lifestyle of couples. In the final step, the designed intervention will be administered as a random clinical trial—on ART candidates, in intervention or control groups in one of Iran University of Medical Sciences hospitals. Afterward, the data’s will be evaluated by using standard questionnaires, that include health-promoting lifestyle questionnaire (HPLII), Beck’s depression inventory (BDI), international physical activity questionnaire—short form (IPAQ-SF), and food frequency questionnaire (FFQ). The statistical analysis will be carried out in SPSS software. During the study, subjects meeting the inclusion criteria were randomly selected and randomized into the intervention and control groups. The health-promoting lifestyle training program will be executed for the intervention group while the standard care program is administered to the control group. The content of this program will be obtained from the consensus opinions of the expert panel. The program includes diet recommendations, physical activity, and stress management. Appropriate time, frequency, duration and number of activities will be considered. Communication with subjects will be possible through private meeting special comfort room. Support to the participants will also be through clinical visits social media, SMS and phone calls. Nutritional changes, physical activity amount, anxiety and stress level, abdominal circumference (AC), and body mass index (BMI) will be measured after the completion of the specified time interval. The initial outcome includes examining chemical pregnancy (2 weeks after the transmission) and clinical pregnancy by ultrasound (6 weeks after). The secondary outcome will be live birth rate. Retrieved oocyte and embryo numbers will also be reported.

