### Registering participants

Clients of the fertility clinics of Akbar Abadi Hospital in Iran University of Medical Sciences will be referred to the research unit after receiving an initial examination by the infertility clinic’s doctors and admitted by infertility midwives or nurses. The study will be described to the consenting participants. The demographic questionnaire and consent form will be completed by the participants and they will ensure of the confidentiality of their information.

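### A constant, published block size of 4 lets anyone who enrols couples and tracks past allocations be certain of up to one third of assignments

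*Protocol article*

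**What the plan says.** All references are to the protocol article.

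- **Block rule.** The section on sampling, randomization and blinding methods opens by saying that "the permuted block randomization will be done using a randomized block design with four blocks". It then states that "75 blocks of 4 will be created based on the sample size of 300 people". The ratio is fixed by "the participants will be divided into two groups per the 1:1 allocation ratio".
- **Issue of allocations.** The same section says "The numbers are placed in sealed envelopes in the order of each block generated" and "Each eligible patient who enters the room is then given an envelope". Assignment is therefore sequential, one envelope per arrival.
- **Setting.** The abstract places the trial "in intervention or control groups in one of Iran University of Medical Sciences hospitals". Under Registering participants, clients of that hospital's fertility clinics "will be referred to the research unit after receiving an initial examination by the infertility clinic’s doctors". No stratification is stated.
- **Arms.** The abstract says "The health-promoting lifestyle training program will be executed for the intervention group while the standard care program is administered to the control group". The Discussion adds that the researcher meets patients face to face in a private room in the infertility clinic, and also keeps contact by text, phone and social networks.
- **Blinding.** The section heading names it, but the text under it describes none.
- **Number randomised.** The randomisation section works with 300 people. The sample size section gives 600 couples, with 150 women and 150 men in the programme arm and the remainder in control.

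**The concern.** In permuted blocks of known, constant size, the end of each block follows from its beginning. A sealed envelope hides the next card but does not stop anyone deducing it from the cards already opened. Here there is a single hospital, no stated strata to split the sequence, and two arms that the person delivering the programme can tell apart.

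The eligibility criteria leave room for judgement. Interest in taking part is an inclusion criterion, and stressful events that disturb psychological status are an exclusion criterion. Someone who foresees the next arm could defer a couple, reorder arrivals or apply a criterion more strictly, all within the written rules. Motivation and prognosis are the traits most open to such steering. They plausibly affect chemical and clinical pregnancy, which the abstract names as the initial outcome. Motivation is also hard to measure, so adjustment for recorded baseline variables cannot be relied on to remove the bias.

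**Working it through.** **Inputs.** Block size 4, 75 blocks, 300 slots and a 1:1 ratio, all from the randomisation section. The observer is assumed to know the block size and every earlier allocation in order.

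**1. The plan's own figure.** 75 × 4 = 300, which reproduces. If four were instead the number of blocks, each would hold 300 / 4 = 75 slots. That is odd and cannot be split 1:1, so the literal reading of the opening sentence is not workable and size 4 is the rule in force.

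**2. Certain allocations with fixed blocks of 4.** There are 6 equally likely orders of two A and two B.
- Slots 1 and 2 are never forced.
- Slot 3 is forced when the first two match. After the first slot, 1 of the 3 remaining places belongs to the same arm, so the probability is 1/3.
- Slot 4 is always forced.

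Expected forced slots per block = 1/3 + 1 = 4/3. Share = (4/3) / 4 = 1/3, or 33.3%. On 300 slots this is 100, and on 600 slots it would be 200.

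**3. Best-guess rate with fixed blocks of 4**, always guessing the arm that is behind:
- Slot 1: 1/2
- Slot 2: 2/3
- Slot 3: (1/3 × 1) + (2/3 × 1/2) = 2/3
- Slot 4: 1

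Sum = 17/6. Divided by 4 this is 17/24 = 70.8%, against 50% by chance.

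**4. Alternatives.** For a fixed block of size 2m, the forced share is [2m/(m+1)] / 2m = 1/(m+1). The best-guess rates for sizes 6 and 8 come from enumerating all orders (20 and 70). The mixed sizes come from simulating 300 lists of 300 slots, with an observer who knows the set of possible sizes and all past allocations but not the order of the sizes.

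| Scheme | Certain | Of 300 | Best guess correct |
|---|---|---|---|
| Fixed 4 (the plan) | 33.3% | 100 | 70.8% |
| Fixed 6 | 25% | 75 | 68.3% |
| Fixed 8 | 20% | 60 | 66.6% |
| Random 4 and 6 | about 5% | about 16 | 69.3% |
| Random 4, 6 and 8 | about 2% | about 6 | 68.1% |

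A larger fixed block leaves many allocations certain. Varying the size removes nearly all the certainty but lowers the best-guess rate by less than 3 percentage points (70.8 − 68.1 = 2.7).

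**5. Imbalance.** If recruitment stops inside a block, the arms can differ by at most half the block size: 8 / 2 = 4 for the mixed scheme, against 4 / 2 = 2 for fixed blocks of 4.

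**The case against.** - **A reader might infer two competing randomisation schemes.** The text does not support this. The same paragraph goes on to give the number and size of the blocks, and the opening phrase is most likely a slip for blocks of size four. That part is a copy-edit.
- **A reader might infer that recruiters will foresee a third of the allocations.** The article does not show this. It does not say who hands out the envelopes. Doctors, midwives or nurses examine and admit, a research unit then takes over, and a statistics consultant produces the list. Nothing establishes that those who refer couples see earlier allocations. That the researcher delivering the programme knows them is a fair inference, but still an inference, as is the open-label status. The 33% and 70.8% are therefore ceilings.
- **Opacity, numbering and custody of the envelopes** are details that a condensed article may leave to the full protocol. Their absence is not held against the plan.
- **The remedy is limited.** Varying the block size hardly changes the best-guess rate. This is correct, and it is why varying sizes alone is not enough.

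What stands is that a constant block size of 4 is a stated rule rather than an omission. It is public, it is used sequentially at one hospital, and no blinding is described to offset it.

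**Conclusion.** The concern holds as a vulnerability of the design. It is not evidence that allocation has been or will be subverted. With constant blocks of 4, up to one third of allocations (about 100 of 300) can be known in advance, and up to 70.8% guessed correctly. Both figures rest on one person having influence over enrolment, knowledge of the block size and a complete ordered record of past assignments. Of these three, the article itself supplies only the block size. The one-third share does not depend on whether 300 or 600 units are randomised, but the count does.

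The correction is worthwhile because it costs almost nothing and the bias it guards against cannot be reliably repaired in the analysis.

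**What to change.** 1. Have the statistics consultant generate the list with randomly varying block sizes, for example 4, 6 and 8, and keep the sizes and their order from recruiting staff.
2. Open each envelope only after consent and the baseline questionnaires are complete and the study number has been written on it. Because the best-guess rate stays near 68%, this step and nondisclosure matter as much as the varying sizes. Release by someone who does not recruit would strengthen it.
3. Editorial: reword the opening sentence of the randomisation section so that four is the size of the blocks, not their number. Drop the statement of constant size once step 1 is adopted.
4. Before regenerating the list, reconcile the unit and number randomised. The randomisation section has 300 people and the sample size section has 600 couples. The arm described there (150 women and 150 men) would fit 300 couples, or 600 individuals, if control is of equal size. Under the present rule, 600 couples would have needed 600 / 4 = 150 blocks.

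**Cost.** One new list. If the named websites do not vary block size, any other routine will do. The downside is a possible final imbalance of up to 4 between the arms, which is negligible at this sample size.

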## Quantitative stage of study

In this stage, the eligible subjects who are interested to participate in the clinical trial will be randomized into intervention or control groups. The target group includes infertile couples undergoing ARTs. The age range of the participants is from 18 to 40 years. They must be able to read and write. It must be their first or second IVF or ICSI session.

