## Sample size and sampling method

The sample size is estimate based on similar studies on the lifestyle of infertile couples [24]. The comparison formula between two ratios will be used at the 95% confidence level The Cronbach’s α of 0.05 and power of 80% will be considered. Finally, 600 couples will be included in the study, of which 150 female and 150 males will be placed in the lifestyle program group and the rest in the control group.

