## Discussion

Health-promoting lifestyle training program comprises a set of consistent activities, such as recommendations and training of skills regarding physical activity, diet, stress and anxiety adjustment methods, sleep hygiene, sleep disorders, adjusting meal portions, improving interpersonal relationships, considering self-actualization, paying attention to psychological health, learning methods of dealing with life problems, and avoiding general health risk factors. A couple is defined as a man and a woman in an emotional and sexual relationship, and there is an economic interaction between them. Couples’ lives and their interactions with each other affect their fertility health. One of the advantages of this study is the inclusion of infertile couples instead of individuals, which can improve the process of promoting health. In addition, they can reduce the pressure caused by infertility issues with collaboration. Another advantage of this study is its cost-effectiveness. Furthermore, couples could support each other and resolve problem together. The researcher will be in contact with the patients through face-to-face meeting in a private room in the infertility clinic or in other ways such as text messages, phone calls and social networking groups, providing daily relevant content and according to their needs and questions to is constantly in touch. This could be another benefit of this study. Furthermore, this study will be conducted by reviewing texts and methods examined up to the present and selecting the method with the highest score. One of the limitations of the study is the limited time for infertile people. Although scattered lifestyle training programs are considered separately for infertile women in Iran, the combined lifestyle training program is rarely used in infertility clinics. We hope that the results of this study will lead to the utilization and improvement of the health of infertile couples.

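### The allocation rule is written for individuals although couples are the target and the unit of the pregnancy outcomes, and nothing keeps spouses in the same arm

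*Protocol article*

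**What the plan says.** Allocation is described only in the Protocol article, section *Sampling, randomization, and blinding methods*, and its units are persons throughout:

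- List size: "75 blocks of 4 will be created based on the sample size of 300 people".
- Division into arms: "with a ratio of 1:1, people will be divided into two intervention and control groups", and again "the participants will be divided into two groups per the 1:1 allocation ratio".
- Handing out: "Each eligible patient who enters the room is then given an envelope".

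Other sections work with couples:

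- *Quantitative stage of study*: "The target group includes infertile couples undergoing ARTs".
- *Discussion*: "One of the advantages of this study is the inclusion of infertile couples instead of individuals".
- *Sample size and sampling method*, on the total: "600 couples will be included in the study". The same sentence then sets out the arms by sex rather than by couple: "150 female and 150 males will be placed in the lifestyle program group and the rest in the control group".
- *Methodology/Design* in the Abstract: the initial outcomes are chemical and clinical pregnancy, and the secondary outcome is live birth. Each occurs once per couple.

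No section says that one envelope covers both partners or that partners share an arm.

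**The concern.** Men and women are both placed in the programme group, and the inclusion criteria (age, literacy) are written for a person. Either partner can therefore be the eligible patient who receives an envelope. Staff who follow the sentence literally could hand one to each spouse.

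A couple with one partner in each arm yields one pregnancy result that cannot be assigned to either arm, or that would be counted in both. The control partner shares a household with someone following the diet, activity and stress programme. The *Discussion* itself argues that partners' interactions affect their fertility health, so contamination follows from the trial's own rationale. It would blur the questionnaire comparisons as well as the pregnancy comparison. Analysis cannot put a couple back into one arm after it has been split, so the unit has to be settled before the first envelope is opened.

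**Working it through.** **1. The plan's own list size.** 75 blocks × 4 = 300 allocations. This reproduces the stated 300.

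**2. Does the list fit the arm sizes?** Three readings, using the 1:1 ratio and the programme arm of 150 women and 150 men (300 people, or 150 couples):

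| Reading | Programme arm | Control arm | Fits 150 women + 150 men in programme? | Fits 1:1? | Fits 75 × 4 allocations? |
|---|---|---|---|---|---|
| 300 people, allocated by person | 150 people | 150 people | No | Yes | Yes |
| 600 couples, 150 in programme and the rest in control | 150 couples | 600 − 150 = 450 couples | Yes | No (1:3) | No |
| 300 couples, allocated by couple | 150 couples | 150 couples | Yes | Yes | Yes |

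Only the third reading satisfies all three conditions. It contradicts two unit labels: people for the 300 in the randomisation section, and couples for the 600 in the sample-size section. Since 300 couples are 600 people, exchanging those two labels would remove both conflicts.

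**3. How often would spouses be split if each drew an envelope?** This is hypothetical; the article does not describe how spouses draw.

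- Same block: a balanced block of 4 has 4!/(2! × 2!) = 6 orderings. Two given positions differ in 4 of them, so P(split) = 4/6 = 67%.
- Adjacent envelopes that straddle two blocks: P(split) = 1/2 = 50%.
- Unrelated positions on a list of 300: P(split) = 150/299 = 50.2%.

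Expected numbers of split couples:

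| Couples enrolled | Unrelated positions (about 50%) | Always the same block (67%) |
|---|---|---|
| 150 (literal 300 people) | 150 × 0.502 ≈ 75 | 150 × 4/6 = 100 |
| 300 (600 people, which would need 600 envelopes) | about 150 | 300 × 4/6 = 200 |

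With 150 couples and 100 split, 50 concordant couples remain, an expected 25 in each arm.

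**4. Limit of the check.** The article names a two-proportion formula with 80% power but gives neither proportion. The power calculation therefore cannot show which total was intended.

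**The case against.** The strongest reply is that the trial already means to randomise couples and the article has mislabelled its units. The allocation section does not mention spouses, and a patient entering the room may be the attending woman or the couple. No stratification by sex is described, so individual randomisation could not fix exactly 150 women and 150 men in one arm in advance, whereas couple allocation does so automatically. The list length fits 300 couples. The *Discussion* describes partners supporting each other, which suggests that they attend the programme together. The article is also a condensed account, and the full protocol may be clearer.

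Most of this stands, and it limits what can be claimed. A reader might infer that the plan intends spouses to draw separately, or that two thirds of couples will be split. The documents support neither. Separate draws are something the wording allows. The 67% needs spouses always to draw within one block, and 100 of 150 rests on a total of 150 couples, which conflicts with the stated programme arm.

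The reply does not remove the point. The article does not merely omit the unit: it states a person-level rule, repeats it, and sizes the list in people. That rule conflicts with the target group, the outcomes and the arm composition given elsewhere in the same document. A probable good intention does not instruct the staff who hand out the envelopes.

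**Conclusion.** The point holds as an internal contradiction over the unit of randomisation. The stated rule allocates persons; the target group, the enrolled unit and the pregnancy and live birth outcomes are couples; and no safeguard keeps partners together. Followed literally with separate draws, the rule would split about 50% to 67% of couples. That range assumes balanced 1:1 blocks of 4 and both partners drawing, and its ends depend on whether spouses' positions are unrelated or in the same block. It measures what the wording permits and does not forecast what the trial will do.

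The mismatch in counts needs no such assumption. A 1:1 list of 300 people cannot fill a programme arm of 300 people, and 600 couples with 150 in the programme arm is not 1:1. The count of 300 couples, 150 per arm, fits the list length, the ratio and the arm composition together.

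**What to change.** In *Sampling, randomization, and blinding methods*, state that:

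- the couple is the unit of randomisation;
- one envelope is opened per couple, after both partners have consented and completed the baseline questionnaires;
- both partners receive the same allocation;
- each of the 75 blocks holds four couples.

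In that section and in *Sample size and sampling method*, replace the 300 people and the 600 couples with one consistent count. On the figures given, 300 couples (600 people, 150 couples per arm) fits. The sponsor should confirm it against the sample-size calculation.

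State that pregnancy and live birth are counted once per couple.

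The cost is a few sentences and a relabelled list, provided 300 couples were already intended. If 300 people (150 couples) were really meant, 300 couples doubles enrolment. If 600 couples were really meant, the list must grow to 600/4 = 150 blocks and the programme arm to 300 couples for 1:1. This should be resolved before allocation starts.

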## Data analysis

The data obtained from the first stage will be analyzed using a meta-analysis tool in RevMan. The data of the clinical trial will be assessed using descriptive and analytical statistics by SPSS software. According to the type of variables, chi-square tests for descriptive variables, determining the average statistical difference of two groups by t-test for independent groups will be used. Regression tests will be performed for the relationship between the variables and the normality of the data will be determined first Findings of the clinical trial will be included in a scientific article following academic standards or will become available in scientific meetings.

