### Inclusion criteria

Interest to participate in the research, age range between 18 and 40 years, ability to read and write, Receiving IVF/ICSI for the first or second times.

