## Data collection instruments

The participant’s information will be collected using approved standard questionnaires. The Health Promoting Lifestyle Profile-II (HPLP-II) is the questionnaire that employed to determine the life status before and after the intervention. It was developed by Walker [32] and its validity and reliability are validated by Mohammadi et al., in Iran [33]. Stress and anxiety will be measured using Beck’s standard inventory [34], and it is validated by Mohammadkhani in Iran [35]. The IPAQ will be employed to measure the physical activity status [36, 37]. The frequencies with which food items are consumed will be assessed using the Food Frequency Questionnaire (FFQ) [37, 38]. Finally, the demographic information will be obtained by a researcher-made demographic questionnaire containing items related to age, weight, height, BMI, occupation, miscarriage, stillbirth, etc. The questionnaire will be completed at the beginning of the first visit. The subsequent assessment will be carried out within the specified time that will choose in expert panel after the intervention.

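### Group comparisons are specified without covariates, which gives up precision on the scales measured at both baseline and follow-up

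*Protocol article*

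**What the plan says.** Under Data analysis, the protocol article names the tests for comparing the two arms: "chi-square tests for descriptive variables, determining the average statistical difference of two groups by t-test for independent groups". No covariate is attached to either test. The section then adds: "Regression tests will be performed for the relationship between the variables". It gives no outcome, covariate or purpose for that regression and does not link it to the treatment effect.

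Under Data collection instruments, HPLP-II is "employed to determine the life status before and after the intervention". A demographic form is described as "containing items related to age, weight, height, BMI, occupation, miscarriage, stillbirth, etc". On timing, "The questionnaire will be completed at the beginning of the first visit", and a later assessment follows at a time the expert panel will choose. The Abstract lists BMI and abdominal circumference among the measurements taken after the programme period.

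The Abstract makes chemical and clinical pregnancy the initial outcomes and live birth the secondary outcome. Inclusion criteria admit couples with "age range between 18 and 40 years" and "Receiving IVF/ICSI for the first or second times". The randomisation section describes permuted blocks of four and names no stratification factor.

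**The concern.** When a score is measured before randomised treatment and again afterwards, the baseline value usually explains part of the variation between people at follow-up. A two-sample t-test on follow-up scores leaves that variation in the error term. A t-test on change scores removes it only partly efficiently. A model with the baseline score as a covariate is at least as precise as either in large samples, and here it needs no new data for HPLP-II or BMI. At stake are wider intervals and lower power on the lifestyle scales for the same couples.

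For pregnancy and live birth, the entry criteria allow a wide age range and two cycle positions, and no stratification is named. A chance imbalance in either would therefore pass into the raw comparison. Whether adjustment would recover much there is a separate question, and it is checked separately below.

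**Working it through.** **Inputs.** The tests, measurement times and entry criteria come from the sections above. Alpha of 0.05 and 80% power come from the sample size section; two-sided testing is assumed. The arm size is also an assumption. The sample size section speaks of 600 couples, with 150 women and 150 men in the programme group. The randomisation section speaks of 300 people in 75 blocks of 4 (75 × 4 = 300), allocated 1:1. I use 150 couples per arm. The article gives no correlation, pregnancy rate or prognostic effect, so those are assumed and shown as ranges.

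**The plan's own figure.** The stated sample size cannot be reproduced or refuted, because the two proportions behind it are not given.

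**Scales measured twice.** Let r be the correlation between baseline and follow-up, with equal variance at both times and one observation per couple. In units of the follow-up variance, the variance of the arm difference is proportional to:

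- 1 for a t-test on follow-up scores
- 2(1 − r) for a t-test on change scores
- 1 − r² for analysis of covariance

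The ratio of covariance analysis to the follow-up t-test is therefore 1 − r². Its ratio to the change-score t-test is (1 − r²) / [2(1 − r)] = (1 + r)/2.

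| r | 1 − r² | Cut vs follow-up test | Equivalent n per arm, 150/(1 − r²) | (1 + r)/2 | Cut vs change test |
|---|---|---|---|---|---|
| 0.4 | 0.84 | 16% | 179 | 0.70 | 30% |
| 0.5 | 0.75 | 25% | 200 | 0.75 | 25% |
| 0.6 | 0.64 | 36% | 234 | 0.80 | 20% |
| 0.7 | 0.51 | 49% | 294 | 0.85 | 15% |

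The cut at r = 0.7 against the follow-up test is 1 − 0.51 = 49%; 51% is the variance that remains. Against the change-score test at r = 0.7 the equivalent size is 150/0.85, about 176 per arm. The percentage cuts do not depend on the arm size; only the equivalent numbers do.

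In power terms, 150 per arm gives the follow-up t-test 80% power at a difference of √(2/150) × (1.960 + 0.842) = 0.323 SD. At that same difference, covariance analysis has 89.9% power at r = 0.5, 93.8% at r = 0.6 and 97.5% at r = 0.7.

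**Pregnancy and live birth.** These have no baseline value, so the formulas above do not apply. Two checks were made with 150 per arm and an assumed control rate of 30%.

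- *Approximation.* The unadjusted test has 80% power at a difference of 15.6 points. If covariates explain a share R² of the outcome variance, n is replaced by n/(1 − R²). R² of 1%, 2%, 5% and 10% gives power of 80.4%, 80.8%, 82.0% and 84.0%.
- *Simulation.* There were 3000 trials per scenario, with 30% against 46% and 40% of couples in a second cycle. The unadjusted test was compared with logistic regression on arm, age and cycle.

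| Odds ratio per SD of age; for second cycle | Unadjusted power | Adjusted power |
|---|---|---|
| 1.0; 1.0 | 82.7% | 82.4% |
| 0.8; 0.8 | 82.4% | 82.6% |
| 0.6; 0.7 | 82.4% | 84.6% |
| 0.45; 0.6 | 82.7% | 86.7% |

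The gain runs from about 0 to 4 points.

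**The case against.** The strongest reply is that a journal article may leave the adjustment model to a fuller plan, that the regression sentence leaves room for one, and that unadjusted tests are valid after randomisation. Part of this stands. The regression sentence is too vague to be read as ruling out an adjusted comparison, and nothing in the article is statistically invalid. But the article does not stay silent on the arm comparison. It names the tests, and a regression on relationships between variables is not stated to be the treatment comparison. Improving a stated method is different from asking for missing detail.

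A second reply is that the article does not say whether the t-test is applied to follow-up or change scores. That is correct, and it is why both comparisons are shown. The larger savings at high correlation belong only to the follow-up reading.

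Three stronger readings are tempting, and the article does not support them.

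- A reader might infer that every outcome loses materially. The initial outcomes and live birth are binary, and the gain there is small.
- A reader might infer that chance imbalance in age or cycle biases the raw pregnancy comparison. The error rate of the unadjusted test already allows for such imbalance.
- A reader might infer that every covariate is already in hand. Cycle number appears only as an entry condition, and no baseline abdominal circumference is stated.

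**Conclusion.** The point holds as one of lost efficiency, mainly on the scales measured at both times. It is clearest for HPLP-II, whose two measurements are explicit. BMI follows from the first-visit form together with the Abstract.

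For correlations of 0.4 to 0.7, the variance given up is 16% to 49% against a follow-up t-test (1 − r² falls from 0.84 to 0.51), or 30% to 15% against a change-score t-test. The upper figure of 51% quoted for the follow-up comparison is the remaining variance at r = 0.7; the cut itself is 49%. For pregnancy and live birth the gain is about 0 to 4 power points.

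All of this rests on assumed correlations, rates and prognostic effects, and the equivalent numbers also rest on 150 per arm. For the binary outcomes the benefit lies in power or in a standardised risk difference. It should not be expected as a smaller standard error of the odds ratio.

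**What to change.** In Data analysis, state that each questionnaire score and BMI measured at both times is compared by a linear model of the follow-up value on arm and its own baseline value. Add a couple random effect where both partners contribute. Include abdominal circumference only if a baseline value is taken.

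As a smaller gain, prespecify for clinical pregnancy and live birth an age-adjusted risk difference with 95% confidence interval, standardised from a logistic model. Add first versus second cycle as a covariate, and keep the raw chi-square test as supportive.

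For HPLP-II, BMI and age the cost is wording only. Cycle number is known at screening and needs one recorded item. Abdominal circumference would need a baseline measurement if it is to be adjusted in the same way.
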